### 3 TRIAL DESIGN

#### 3.1 Intervention study

This is a primary care based, multicentre, 2-year (including a 26-week intervention), two-arm individually (1:1 ratio) randomised controlled, parallel group feasibility trial.

Patients with type 2 diabetes will be randomised to current care with individually tailored mobile device-based intervention encouraging and supporting them in developing a habit of taking their medication as intended and providing hints and tips to help them with other aspects of living with the condition (treatment arm) or to current care with the addition of infrequent non-health related messages (usual care arm).

The trial team will be blinded as to participant allocation to either the intervention or control arm. Investigators conducting qualitative interviews and focus groups with patients in the intervention arm will not be blinded to participant arm allocation but systems will be implemented to avoid clinicians or the trial team becoming aware of allocation status for individual participants. [See *Appendix A for study flowchart*].

Participants will receive messages for 26 weeks (approximately six months) from randomisation to final follow-up and remain in the trial for a further 18 months with data collected from their medical record. After the initial screening and eligibility check, informed consent will be obtained.

All participants will be followed-up at the end of the follow-up period post randomisation to collect questionnaire information (same as for baseline) and follow-up measures (same data collected for baseline). [See *Appendix B for a detailed schedule of procedures*].

##### 3.1.1 Process evaluation (Cohort 1 - trial participants)

The process evaluation will consider mechanism, context and implementation using both quantitative and qualitative methods. The purpose of the evaluation will be to decide if any of the messages, or behaviour change techniques should be omitted prior to the main trial. Participants will be purposefully selected from the feasibility trial and invited to take part in qualitative interviews and post-follow up debriefing phone calls to share their views on the messaging system, insight into how it was implemented in daily life, identify issues around potential attrition and inform final procedures for the main trial (see *Section 4.1 Qualitative work with study participants* for further information). Up to 30 patients will be recruited.

If there is no change in the quantitative measure of proposed mechanisms, and there is qualitative evidence that certain behaviour change techniques (BCTs) and/or messages are disliked by participants, or have a negative impact on implementation these will be omitted prior to the main trial.

### **3.2 Interviews with Health Care Professionals from GP Practices (Cohort 2)**

Finally, between 12 and 30 staff from GP practices taking part in the trial (the number based on considerations of data saturation) will also be invited to take part in focus groups and/or qualitative interviews to share their experience of recruiting for this trial, how the intervention was implemented in routine clinical care etc. (see *Section 4.2 Focus Group Work with Healthcare Professionals* for further information).

### **3.3 Treatment of Cohort 1 participants**

#### **3.3.1 INTERVENTION GROUP - Tailored mobile-phone messaging system**

The intervention consists of brief, health related messages delivered via SMS text-message with content based on participant feedback received during formative work for this trial. The type of messages sent to participants are based on frequency of prescriptions issued to participants and other forms of real-time feedback from participants.

The intervention is a system with the following components (Appendix C provides a detailed description of the intervention components and their development).

- i. Receipt of automated SMS text-messages relating to diabetes management and use of medicine.
- ii. The library of messages includes different types of message using different behaviour change techniques (see appendix C for further details of the types of messages in relation to behaviour change techniques) to target health-related behaviour change relating to use of medicines, as well as messages targeting other aspects of diabetes care (e.g. diet and exercise).
- iii. The types of messages sent (tailoring of messages) will be made more appropriate to individuals based on time since starting new medication and smoking status.
- iv. Types and content of messages will also be linked to the records of prescribed medication details, appointment details and blood test results.

Frequency of messages using a particular type of behaviour change technique will be modifiable based on interactive automated messaging about a participant's response to individual messages received.

- v. Participants will be offered up to four text-messages per week with an average frequency of three per week.
- vi. The style of messages will be patient-centred and will encourage patients to seek further associated information (including the use of links to selected external websites e.g. Diabetes UK).

The system for sending SMS text-messages is based on an NHS compliant computer network (see Appendix C).

#### **3.3.2 CONTROL GROUP - Usual care**

Participants assigned to usual care will be signed up to receive non-health related messages at a frequency of approximately one every four weeks. Care will otherwise not differ from usual care.

#### **3.3.3 Potential risks and benefits of the tailored mobile-phone messaging system**

We do not anticipate harms from using this system. The messages are carefully designed to avoid requiring specific changes in management, rather they are aimed at supporting behaviours

around use and maintenance of recommended treatments. We will make standard recommendations about safety in use of mobile phones and devices in the PIS.

Participants will be able to interact with the system. This will give them the opportunity to influence the types and frequencies of the intervention messages to their individual needs and preferences. They will also be given the option to pause and restart the messages and will be able to contact the trial team at any time if they would like to stop receiving messages or withdraw from the trial.

The major benefit of the intervention would be the information and advice participants receive about their condition. This may increase their understanding of type 2 diabetes and provide support with managing their condition.

### **3.4 PARTICIPANT IDENTIFICATION**

#### **3.4.1 Trial Participants – Cohort 1**

Participants are people with type 2 diabetes registered with a UK general practitioner (GP). Eligible patients should meet all of the inclusion and have none of the exclusion criteria listed below. Any queries regarding patient eligibility should be directed to the trial team prior to randomisation. No more than one individual within the same household will be recruited and participants will be asked not to share messages.

##### **3.4.1.1 Inclusion Criteria**

- Participant is willing and able to give informed consent for participation in the trial.
- Male or Female,  $\geq 35$  years of age.
- Type 2 diabetes.
- Taking oral glucose lowering treatment, blood pressure lowering treatment or lipid lowering treatment either alone or in combination.
- Has started one or more of these medications or had a change in one of these medications within the last three months.
- Has access to a mobile phone and is able, if necessary with help (e.g. relative, friend, neighbour), to send, understand and retrieve brief SMS text-messages in the English language.
- The participant's practice is participating in the trial.

##### **3.4.1.2 Exclusion Criteria**

The participant may not enter the trial if ANY of the following apply:

- Female participant who is pregnant, within three months post-partum or planning pregnancy during the course of the trial.
- A serious medical condition that, in the opinion of the investigator, makes them ineligible.
- Insulin treatment without also concomitant use of oral glucose lowering treatment.
- Patient has been admitted to hospital within the last three months for hyper- or hypoglycaemia (self-report)
- Another person in the household already participates in this trial

#### **3.4.2 Staff from GP Practices – Cohort 2**

- Inclusion criteria – staff are aware of the text-messaging intervention and have contact with patients or the management of patients with type 2 diabetes (see *Section 4.2 Focus Group Work with Healthcare Professionals* for further information).

- Participant is willing and able to give informed consent for participation in the study.
- No exclusions.

### **3.5 TRIAL PROCEDURES**

*See Appendix B for a summary of the trial procedures.*

#### **3.5.1 Recruitment procedures - Cohort 1**

Potential participants will be identified primarily through general practices across the UK. Alternative routes to approach potential participants in areas to support practices in recruiting patients e.g. condition specific mailing lists, databases of 'research-interested' people, pharmacies, community centres, libraries, other public areas, social media, recruitment advertisements in condition-specific charities, local news outlets, GP practice websites, GP practice waiting areas, trial website etc. will be considered and used if necessary to explore alternative modes of engaging people and encouraging them to consider checking whether their practice is taking part in the trial. To raise awareness about the trial and opportunities for participation, a short information leaflet may be provided to patients via a variety of methods including post, e-mail, displayed at sites' waiting areas, given to patients by a practice team member and the alternative routes described above.

Healthcare professionals will screen their type 2 diabetes clinic lists for potentially eligible patients and also identify participants attending opportunistically. Where possible, health care professionals may be asked to screen their clinic lists and mail-out to potentially eligible patients. Following an initial mail-out, subsequent searches may be carried out to identify newly eligible patients. Newly eligible participants may also be contacted by a number of methods (including phone, letter, email or text-message), by the practice team up to three times.

People who may be interested in taking part in the trial will be asked to send their name by SMS text-message to the trial team to express this interest. If potential participants have any difficulties in registering their interest in the trial in this way, they will be able to call a Freephone trial telephone number or email the trial team and will receive support in registering as required. Following their verbal consent, people who contacted the trial team will be given the opportunity to discuss the trial further by telephone and, if there is interest and the potential participant is willing, carry out a screening interview to collect data about eligibility.

#### **Recruitment of Healthcare Professionals (Cohort 2)**

See section 4.2 for information on identification and consent of healthcare professionals.

#### **3.5.2 Screening Assessment**

Following a participant's expression of interest (via text, phone or email), provision of further information about the study and screening for eligibility, may take place within the same phone call or a subsequent contact with the patient may be arranged, if needed, to answer any questions they may have.

Participants will be able to ask their healthcare professional or the members of the trial team any questions they have and the team will confirm if they are eligible to take part in the trial prior to completing informed consent.

Eligible patients will need to meet all the inclusion criteria and not meet any of the exclusion criteria described in sections 3.4.1.1 and 3.4.1.2.

Participants that have been found ineligible due to their GP practice not being a recruiting practice may be screened again, above provision of verbal consent to be approached if their practice signs up to the trial during the recruitment period.

### 3.6 Informed Consent

Participants will be provided with the participant information leaflet and have to sign a consent form prior to any trial procedures being performed. Participants will personally sign, write their full name and date the consent form, before any trial specific procedures are performed (or complete with their full name and personal password (also referred to as access code), if done electronically).

Participants will be given as much time as they wish to consider the trial information (at least 48 hours before any subsequent contacts are made to confirm receipt of the forms and answer any questions the participant may have).

Participants will be advised that they may be contacted throughout the 26-week follow-up period should any issues arise (e.g. the participant is not able to receive messages), and that the last contact with the team will be at 26 weeks ( $\pm 4$  weeks) to collect information from the follow-up questionnaires. They will be advised that we will ask for information from their medical records about medication, blood tests and other related health data for up to two years. Participants will be informed that if they agree they may be invited to participate in a qualitative sub-study during which additional contacts may be made (see section 4.1).

It will be clearly stated in the participant information leaflet that the participant is free to withdraw from the trial at any time for any reason without that affecting their care or legal rights and with no obligation to give the reason for withdrawal. However, as one of the trial objectives is to test "participants' willingness to be randomised", those who withdraw will be asked a question whether they decided to withdraw because they were not randomised to the intervention group.

If completing consent online, the participant will be asked to enter their full name, and their password (provided by the trial team) to verify their identity and access the participant information leaflet and e-consent form. Informed consent for those completing paper-based forms will be obtained by means of a participant dated signature.

The participant will be required to agree to each statement on the electronic consent form in the same way that they would complete the paper based consent form, and write their full name and date before submitting it. The combination of personal password, full name and date will form the electronic signature for each person participating in this trial.

A copy of the signed informed consent will be provided to the participant via email or post according to the Nuffield Department of Primary Care Health Science's Information Governance toolkit. A second copy will be provided to the participant's GP to be kept with their patient's medical records.

Due to the low risk posed by the nature of the trial, participants may be consented and have their baseline assessments completed on the same day as the day of expression of interest. Participants can subsequently withdraw consent at any point in the trial without penalty having taken more time to consider participation.

### 3.7 Randomisation, blinding and code-breaking

A secure web-based randomisation system will be provided by the Oxford Primary Care Clinical Trials Unit (PC-CTU) using the Sortition software programme. Participants will be allocated to one of the two arms: Intervention Group - usual care with the support of a mobile based intervention or Control Group - usual care with the addition of non-health related messages on a 1:1 basis. Allocation will be carried out using a non-deterministic minimisation algorithm to ensure intervention groups are balanced for important baseline prognostic and other factors: study site, age ( $<65/\geq 65$  years), gender (M/F), duration of diabetes ( $<5/\geq 5$  years), number of medications ( $<5/\geq 5$ ).

If the web-based randomisation system is not accessible, allocation will be carried out following emergency randomisation procedures outlined in the trial working instructions.

Participant allocation will not be formally blinded to healthcare professionals but to avoid contamination around outcome measurement no records of allocation outwith the trial database will be made. As this is a low risk feasibility trial, unblinding procedures are unlikely to be needed. However, in the event of a participant's clinical condition necessitating breaking the code, this will be done according to the relevant PC-CTU SOP or trial specific working instruction and the group allocation will be sent to the chief investigator, site principal investigator or patient's GP.

### **3.8 Baseline Assessment**

Participants will be invited to access the participant information leaflet, consent form and baseline questionnaires on the trial website. Each participant will be given a unique personal password to allow access to the trial website. A unique personal password in combination with the volunteer's full name will form part of their electronic signature that will enable them to log in to the trial website and complete their baseline forms (including participant information leaflet, consent form and baseline questionnaires).

Alternatively and on request, participant information leaflet, consent form and baseline questionnaires will be sent by post to potential participants. Members of the trial team will be available to offer support, guidance in using the online system and further information at the same time as completing the forms, if needed.

A Freephone number to contact the trial team will be made available. The participant will be able to contact the trial team whenever needed to ask any questions they have, including questions they have prior to completing their consent form.

#### **3.8.1 Baseline assessment procedures**

After eligibility is confirmed and consent has been taken, the following procedures will take place:

- Contact details will be collected on the phone, or online and will be updated where there is information missing from previous contacts.
- Participant completion of baseline questionnaires. These are:
  - MARS self-report scale (Questions about using your medicines)
  - EQ-5D-5L (Health status EQ-5D-5L)
  - A measure based on health psychology theory and the technology acceptance model. (Ideas and concerns about your diabetes treatment)
  - Healthcare utilisation record (Health services use)
  - Specific questions about experience of diabetes education, presence of a carer and their role in dose administration, duration of diabetes, if the pharmacy used by the participant automatically requests patient's medication from surgery, self-reported level of education, smoking, age, gender, ethnicity, NHS number, Date of Birth, familiarity with mobile phones and computers, and details of current mobile phone including contract.

All self-report data will be collected either on paper forms or electronically.

Participants will be contacted at least 48 hours after they have been provided with their baseline forms to confirm they have received them.

If the forms have not been submitted or received by the trial team 7-14 days from the date they were sent by the team, further contacts will be made.

- The following baseline measures will be obtained from the participant's medical record and provided to the trial team. For the period of 15 months prior to recruitment: HbA1c,

systolic and diastolic blood pressure, total and HDL cholesterol, weight, height, current medication and prescriptions for diabetes drugs (glucose lowering, blood pressure lowering and lipid lowering. Previous occurrence of myocardial infarction, stroke, Transient Ischemic Attack (TIA), heart failure, peripheral vascular disease and renal failure. Data collection will be through one of the following routes: provision of a medical summary by the GP practice team, or a baseline CRF completed by a nurse or facilitator or a trial team member visiting the surgery.

### **3.8.2 Follow-up (data collection)**

Follow-up will last for 26 weeks after randomisation. For ease of reference, all patient facing documentation will refer to this period as 'six months'. To address any issues that may arise (e.g. the participant is not able to receive messages), an unscheduled contact may be made during the 26 week follow up period if required.

Participants will be asked to complete the following questionnaires at 26 weeks ( $\pm$  4 weeks) following randomisation:

- MARS self-report scale
- EQ-5D-5L
- A measure based on health psychology theory and the technology acceptance model.
- Healthcare utilisation record

The 26-week follow-up questionnaires will be posted to the participant or a link will be given to them via email. If the participant's follow-up questionnaires have not been received one week after the due date, the trial team will contact the participant to remind them to complete these online or on paper. Multiple attempts will be made within the determined window ( $= \pm$  4 weeks).

If participants choose to complete the 26-week measures online, they will be required to log in to the electronic questionnaires using the same electronic verification process used at baseline assessment.

Follow up data will be obtained from the medical record and provided to the trial team for the period of 26 weeks after recruitment: HbA1c, systolic and diastolic blood pressure, total and HDL cholesterol, weight, height, current medication and prescriptions for diabetes drugs (glucose lowering, blood pressure lowering and lipid lowering). Data collection will be through one of the following routes: provision of a medical summary provided by the GP practice team or a 26-week notes review CRF completed by a nurse or facilitator or a trial team member visiting the surgery.

### **3.9 Long term follow up**

We will obtain consent to collect routine medical data from participants' GP notes two years after randomisation. This will allow exploratory data to be obtained about longer term outcomes to inform the analysis of data from future studies.

### **3.10 Discontinuation or withdrawal of participants from trial**

Each participant has the right to withdraw from the trial at any time. In addition, the Investigator may discontinue a participant from the trial at any time if the Investigator considers it necessary for any reason including:

- Pregnancy
- Ineligibility (either arising during the trial or retrospectively having been overlooked at screening)
- Significant protocol deviation

- Significant non-compliance with trial requirements
- Disease progression which renders further data collection inappropriate
- Withdrawal of consent for data collection
- Loss to follow up

An intention-to-treat analysis will be adopted, so if a participant withdraws from the trial, their data up to that point will be used in analysis.

The reason for withdrawal will be recorded in the relevant CRF as per the PC-CTU SOP

Withdrawn participants will not be replaced.

Participants may decide to stop receiving text messages. **This does not constitute withdrawal from the trial.** Data collection will continue unless declined.

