## 6 STATISTICS

### 6.1 Description of Statistical Methods

The analysis will be carried out once the final patient has completed their 26-week follow up. An intention to treat approach will be used, where all participants randomised will be included in the group to which they were allocated, regardless of intervention received. The results of the primary and secondary objectives will be presented descriptively using proportions and 95% confidence intervals.

The primary outcome will be the number of patients recruited and randomised as a proportion (with 95% confidence interval) of the target recruitment number.

Secondary outcomes, including loss to follow up (%), withdrawals (%) and completeness of data collection for various outcomes (%), will be presented overall and separately by treatment group.

Exploratory outcomes (changes in primary and secondary measures to be used in the main trial) will be analysed using an intention to treat approach. Continuous outcomes will be analysed using an analysis of covariance adjusting for minimisation factors. Results will be presented as a difference in means with 95% confidence interval. Binary outcomes will be analysed in a similar way using log binomial regression models (adjusting for minimisation factors). Results will be presented as relative risks with 95% confidence intervals.

A detailed statistical analysis plan will be prepared prior to data lock.

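### Section 3.10 implies that follow-up ends when an investigator discontinues a participant who still consents, which sits badly with the ITT rule in section 6.1 and feeds into the retention outcome

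*Protocol*

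**What the plan says.** Section 3.10 of the protocol gives a broad power: "the Investigator may discontinue a participant from the trial at any time if the Investigator considers it necessary for any reason including" a list of reasons. The list includes ineligibility found late, "Significant protocol deviation", "Significant non-compliance with trial requirements" and "Loss to follow up". Withdrawal of consent for data collection is a separate item, and so is disease progression that makes further data collection inappropriate.

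The section then adopts intention to treat and draws a consequence from it: "so if a participant withdraws from the trial, their data up to that point will be used in analysis". It closes by saying that a participant who stops the text messages has not withdrawn, and that "Data collection will continue unless declined".

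Section 6.1 states the analysis rule differently: "all participants randomised will be included in the group to which they were allocated, regardless of intervention received". It reports losses and withdrawals as percentages, overall and by group, and treats the comparisons of main-trial measures as exploratory.

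Sections 3.8.2 and 3.9 and Appendix B place the follow-up questionnaires at 26 weeks and the GP-record extractions at 26 weeks and two years. Section 6.2 sizes the trial on 80% follow-up of 200 participants, with a 95% confidence interval of 73.8% to 85.3%.

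**The concern.** Using data up to the point of exit is not what intention to treat means. It describes truncated follow-up. The discontinuation in section 3.10 is from the trial, not just from the messages, and several of the listed reasons (non-compliance, deviation, late-found ineligibility) are ones after which an intention-to-treat analysis calls for follow-up to go on.

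Two things are at stake. First, obtainable data may be lost. HbA1c, blood pressure, cholesterol and prescriptions come from the GP record and need no further contact with the participant. Section 3.6 has participants told that record data will be sought for up to two years. Second, retention, completeness of clinical data and obtainable prescribing data are secondary outcomes of this feasibility trial. If an investigator's decision ends follow-up, the retention figure no longer measures only the willingness of participants to be followed up, which is the stated objective.

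**Working it through.** **Does discontinuation end data collection?** The protocol does not say so outright. Four features of section 3.10 point that way:

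1. Continued collection is promised only for participants who stop the messages, and the promise is set against withdrawal. The natural reading is that leaving the trial does stop collection.
2. Withdrawal of consent for data collection is one item among several, so the other items can apply to someone who still consents.
3. The disease-progression item treats discontinuation as the end of data collection.
4. The heading pairs discontinuation with withdrawal, but the rule on data mentions only withdrawal. Either that rule also covers investigator-led discontinuation, or there is no rule for it.

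**Which outcomes are exposed?**

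- Recruitment and randomisation (primary): complete before any discontinuation, so unaffected.
- Historical record data for the 15 months before entry: unaffected.
- 26-week questionnaires: taken only at baseline and 26 weeks, so a participant removed earlier has no follow-up value.
- 26-week and two-year GP-record data: lost if extraction stops.
- Retention and completeness: changed directly.

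**The plan's own figure.** The exact (Clopper-Pearson) 95% interval for 160/200 has lower limit Beta(0.025; 160, 41) = 73.8% and upper limit Beta(0.975; 161, 40) = 85.3%. This reproduces section 6.2. The Wilson (73.9% to 85.0%) and Wald (74.5% to 85.5%) intervals do not match.

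**Effect on retention.** The documents give no discontinuation rate, so k is an assumption: the number of the 160 who would have been followed up but are discontinued by the investigator. With all 200 randomised in the denominator, follow-up = (160 − k)/200, so each case costs 0.5 percentage points.

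| k | Follow-up | Exact 95% CI |
|---|---|---|
| 0 | 160/200 = 80% | 73.8% to 85.3% |
| 4 | 156/200 = 78% | 71.6% to 83.5% |
| 10 | 150/200 = 75% | 68.4% to 80.8% |
| 20 | 140/200 = 70% | 63.1% to 76.3% |

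The estimate passes below 73.8% at k = 13, since 147/200 = 73.5% while 148/200 = 74.0%.

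The denominator matters too. If k participants who would have been lost anyway were dropped from it, which section 6.1 does not allow, the figure would rise: 160/190 = 84.2% for k = 10 and 160/180 = 88.9% for k = 20.

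**Effect on the between-arm comparison.** If a share f of one arm is missing for this reason and differs by d SD from that arm's mean, the bias is about f × d. With assumed f of 5% to 10% and d of 0.25 to 0.5 SD, it runs from 0.05 × 0.25 = 0.0125 to 0.10 × 0.5 = 0.05 SD. The standard error of a difference in means with 80 per arm is √(2/80) = 0.16 SD. The bias is small beside it.

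**The case against.** The strongest reply is that section 3.10 never says data collection stops. Its sentence on data commits to keeping what has been collected, speaks of a participant who withdraws, and does not contain the word *only*. Nobody is excluded from the analysis set or moved between arms. The result is missing data, and the handling of missing data is commonly left to the SAP. This stands in part: the conflict with section 6.1 is a tension, not a literal contradiction. But a SAP cannot recover data that sites have stopped collecting.

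A reader might also infer that the rule removes poor adherers and so selects on the outcome, differently in the two arms. The documents do not support this. The listed reason is non-compliance with trial requirements, not with medication. Stopping messages is not withdrawal, and section 3.3.3 offers pausing as an option. Section 3.1 blinds the trial team. Healthcare professionals are not formally blinded, but section 3.7 keeps allocation out of all records except the trial database. Removing exactly the lowest 5% to 10% of one arm would shift a normal mean by φ(z)/(1 − p) = 0.11 to 0.20 SD. That assumes a one-sided effect and perfect selection on the outcome, so it is a ceiling and not an estimate.

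It is fair, too, that someone discontinued for loss to follow-up is already not retained. That item cannot distort a retention rate over all randomised; it matters only for GP-record data that were still obtainable.

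Finally, reasons for withdrawal already go on the CRF, and withdrawals are reported by arm. Section 6.1 does not, however, separate investigator-led from participant-led exits.

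**Conclusion.** The point holds as a tension between sections 3.10 and 6.1 with a practical consequence. Read as a whole, section 3.10 implies that follow-up ends for some participants who still consent. Obtainable 26-week and two-year data would then be missing, and investigator decisions would enter the retention and completeness outcomes.

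The size depends on a removal rate that the protocol does not give. On the assumption that everyone removed would otherwise have been followed up, 10 removals cost 5 percentage points and 20 cost 10, taking follow-up to 70% against a stated lower limit of 73.8%. Fewer removals, or removal of participants who would have been lost anyway, would cost less.

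It would go too far to conclude that the rule biases the trial's results. The between-arm comparisons are exploratory, any bias in them is possible but not shown, and under the assumptions above it is about 0.01 to 0.05 SD. The primary recruitment outcome and the historical-record outcome are untouched.

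**What to change.** Reconcile section 3.10 with section 6.1:

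- State that after discontinuation for non-compliance, protocol deviation, late-found ineligibility or loss to follow-up, data collection continues unless the participant withdraws consent for it. At the least this means the 26-week and two-year GP-record extraction, plus the 26-week questionnaire attempt where contact is possible.
- Leave the disease-progression item to the investigator's judgement, as now.
- Replace the clause that explains intention to treat as data up to withdrawal with the definition in section 6.1.
- Keep all randomised participants in the retention denominator.
- Report investigator-led discontinuations separately from participant withdrawals, by arm.

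The change concerns data collection, not treatment. It costs protocol wording, one reason code on the CRF, and a few more record extractions from practices that already supply data.
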